### Donation declaration

Any organs/tissue used for ATT-Heart will be sourced ethically and any organs/tissue used will not have been sourced from executed prisoners or prisoners of conscience or other vulnerable groups.

In this study, the donated hearts are from deceased donors. The National Organ Retrieval Services, part of NHS Blood and Transplant, are a specialist team that will manage the procurement process, obtaining and preparing hearts for transplantation. This includes retrieval, characterisation, preservation and transport arrangements. The study team will not be involved in this process and it is independent of the study.

### Additional consent provisions for collection and use of participant data and biological specimens

Thymus tissue is usually routinely excised during heart transplant surgery and discarded. However, thymus tissue is rich in Tregs and hence can be considered a useful source for generation of the Treg product for the purpose of this study. The thymus tissue for ATT-Heart study participants, who consent to enter into the study, will be retained and transported to the GMP Facility to manufacture the Treg cell product (TR006).

ATT-Heart involves the collection and processing of biological specimens from participants (including blood and tissue samples from routine clinical procedures such as clinical blood tests and heart biopsy samples, as well as research samples).

Consent (and where appropriate, assent) will also be obtained for the retention and use of patient samples in related future research.

### Provision for participant care

Study participants will be considered as ‘live autologous thymus donors’, and will follow the same pathway as standard care heart transplant recipients before, during and after heart transplant surgery and thymus tissue procurement. Study visits have been designed to follow the standard post-heart transplant recipient care pathway.

ATT-Heart participants will attend GOSH for additional study visits (as TR006 dosing includes safety monitoring on the day of dosing and also an overnight stay to oversee the participant post-dose, and on Safety Follow-up Day 14 for more safety monitoring post-dose). There will also be remote safety monitoring carried out after dosing (as part of Safety Follow-up Days 2–13).

Team members will check at each visit with patients/parents/guardians that their consent to ATT-Heart is still valid. Patients will be presented with the option to continue to remain in the study, or withdraw, prior to IMP dosing and follow-up. Each participant has the right to withdraw from the trial at any time. Participants will continue on study until they express their wish to withdraw.

The participants and the parents/guardians of the participants who wish to withdraw from the study will be asked to confirm whether they are still willing to provide data collected as per routine clinical practice at visits. Their follow-up clinical care will be as per routine practice.

### TR006 manufacture

TR006 contains Tregs isolated from thymus tissue, which are polyclonally expanded in vitro, then administered as a single-use named patient therapy as an intravenous solution. As per our GMP compatible protocol,^46^ thymus tissue will first undergo mechanical digestion and then Treg isolation. This will require depletion of CD8^+^ cells followed by enrichment for CD25^+^ cells. The CD4^+^ CD25^+^ cell populations will be expanded for up to 23 days to obtain the Treg dose required for each patient. The polyclonal expansion will be undertaken in the presence of anti-CD3/CD28 beads, rapamycin and IL2.^46^

The final cell product will undergo a robust quality check assessment (immunophenotyping, potency, sterility testing, mycoplasma, endotoxin and viability testing) and the criteria to release for administration will in particular require ≥50% FOXP3^+^CD25^+^ expression of cells and >60% Treg suppressive ability at a 1:1 and 1:10 ratios of Tregs: T effectors. TR006 will remain cryopreserved for storage and delivery to GOSH. On the ward, the cell product will be handled by appropriately trained staff and thawed at the bedside prior to intravenous administration through a syringe pump by the research team.

### Intervention description: dose escalation strategy

Participants will receive a 10 mL single dose of TR006 at 1–3×10^6^ TR006/kg or at 5–10×10^6^ TR006/kg.

A single ascending dose design will be followed with groups of three patients in three cohorts. The first cohort of three patients will receive a lower dose of 1–3×10^6^ Tregs cells/kg and if no Dose-limiting Toxicities (DLTs) occur, then the second cohort (of three patients) will be given a higher dose of 5–10×10^6^ Treg cells/kg. The third cohort of three patients will receive the highest tolerated dose of Tregs from the second cohort (up to a maximum of 10×10^6^ Treg cells/kg).

These dose ranges were selected to match what we estimate to be the minimal anticipated biological effect doses based on the ThRIL and ONE study.^17 20^ Of note, the dose escalation schedule in ATT-Heart is more conservative than previous Treg trials conducted in children in Poland,^14^ the USA^16^ and Spain.^21^ However, as this is the first clinical trial in the UK with thymus derived Tregs, our priority is to determine safety of the IMP, as agreed with the Medicines Healthcare products Regulatory Agency (MHRA).

We will monitor biological activity of Tregs in vivo in this study. However, we plan to conduct further dose escalation and formally investigate biological efficacy in a future phase II trial if this trial confirms initial safety in patients and feasibility of manufacturing initial dose ranges.

### Provisions for post-trial care

All trial participants will be patients registered with GOSH for provision of their post-transplant care. Once the participant’s involvement in the study is over, they will continue to receive their usual post-transplant care (which includes lifelong medical follow-up).

### Study outcome measures

#### Primary endpoints

The safety profile of the IMP is a key endpoint. DLTs such as presence of non-specific cytokine release, febrile episodes, hypersensitivity reactions, haematological derangement, biochemical imbalances and organ rejection that may occur up to 4 weeks post-IMP administration will be recorded. Clinically, these will be managed as per local guidelines. We will also record any suspected or confirmed DLTs that may occur beyond 4 weeks of IMP administration.

#### Secondary endpoints

Feasibility of obtaining thymus tissue and expanding Tregs to an adequate dose (1–10×10^6^ cells/kg) as planned for the study will be documented for each patient entering the trial.To investigate the clinical responses to TR006, tests to determine the cardiac function, renal function and early CAV development (by recording the Minimal Intimal Thickness) by IVUS at protocol set time points. Furthermore, incidence of clinical morbidity events such as suspected or confirmed donor organ rejection, frequency of infection, hospitalisation events, immunosuppressive drug doses, transplantation outcome and mortality within 24 months of the IMP administration will be documented.To investigate the effect of TR006 on the immune system of the recipient, blood samples will be collected at different time points before and after TR006 infusion over the safety follow-up period. Brief details of the analysis techniques are outlined in table 1.

**Table 1 T1:** Summary of immuno-monitoring analysis for ATT-Heart

Parameters measured	Method/test
Evaluation of circulating, proliferating, naïve and memory CD4^+^ and CD8^+^ T cell subsets and recent thymic emigrants in peripheral blood. Longitudinal comparisons will be conducted across different visits to assess the pharmacodynamic effects of TR006 based on the administered dose.	Flow cytometry
The deep phenotyping aims to comprehensively monitor 37 immune cell subsets and elucidate the modulatory effects of TR006 infusion on the patient’s immune landscape. Additionally, the study seeks to identify predictive immunological signatures associated with the early onset of CAV.	Mass cytometry (CyTOF)
Donor-specific antibodies: to assess risk of potential future antibody-mediated rejection.	Luminex
VEGF-C and A platelet factor 4: serum predictive factors for CAV development will be recorded.	ELISA
The assay of alloreactivity aims to measure T cell responses against donor antigens (and third-party antigens, as a control) to assess whether Treg therapy has specifically decreased the response against donor antigens, as previously published.^20^	Pleximmune test
Applying 5′ scRNA-seq to both the infused Treg product and the patients’ peripheral blood will enable clonal tracking and identification of cell therapy-derived populations over time.	Single cell RNA sequencing (scRNA sq)
Quantifying TH1/2/17 related cytokine serum levels to quantify cell-mediated or humoral-mediated immune responses to graft following TR006 infusion.	Multiplexed immunoassays (Meso Scale Discovery)
Histological signs of organ rejection in endomyocardial tissue biopsy by determining type of graft infiltration and inflammation.	(Standard of care) Immunohistochemistry staining
Assess composition and functionality of immune infiltrates and modulation of resident immune cells.	Spatial proteomic and transcriptomics

CAV, cardiac allograft vasculopathy; CyTOF, Cytometry by time of flight; VEGF, Vascular Endothelial Growth Factor.

In terms of the broader impact of our research, our clinical grade thymus derived Treg expansion protocol^45 46^ for producing functional and stable Treg therapy even after cryopreservation has been developed for this trial. As we plan to include children from a broad age range (6 months–16 years), the results from this trial may confirm feasibility of generating adequate doses with our Treg expansion protocol for older children and adolescents with smaller thymus tissue due to the expected age-related atrophy of thymus.

Producing Treg cellular therapy that can be cryopreserved and retain stability could be of benefit for a future ‘off the shelf therapy’. Clinical outcome data as well as immune-monitoring data from this trial will support identification of the dose at which biological efficacy is seen ahead of a phase II study in the paediatric heart transplant cohort. Patient and family reported data will also help shape a future trial design and conduct.

### Immuno-monitoring specific integrative data analysis plan

We will continue to prioritise Treg enrichment because our primary mechanistic questions are whether Tregs can be tracked by T Cell Receptor (TCR) clonality over time and how their phenotype and state changes post-infusion. To that end we will run 10× Chromium X 5’ captures on FACS-enriched Tregs with paired TCR VDJ. This preserves depth on a rare population and gives a robust clonotype map.

To provide the broader immune context, we will also perform whole-PBMC single cell (sc) RNA-sequencing with Cellular Indexing of Transcriptomes and Epitopes (CITE)-sequencing. We will employ cell hashing to multiplex samples and control cost. CITE-sequencing and TCR-sequencing will be generated from the same 10× capture so this approach will not compromise gene-expression depth on the enriched Treg runs. Further details on the time points are below.

We will use endomyocardial biopsies at day 14, month 3 and month 6 (ie, 3 months post-Treg infusion) and profile them by 10× Xenium. From each biopsy, we will focus on analysis of regions around small vessels to quantify endothelial activation, perivascular myeloid and lymphoid niches, fibroblast and matrix programmes and the presence of FOXP3+T cells. We will place control and Treg arm biopsies on the same slide to control for batch effects.

The primary clinical outcome is coronary allograft vasculopathy progression measured by IVUS (or coronary angiography in younger children) as the change in mean intimal thickness from month 3 to month 12, together with the prespecified CAV grade at month 12. Although CAV is defined in the coronary arteries, it is driven by immune and stromal processes that are reflected in the myocardial microvasculature. The spatial assay reads out those processes in situ. We will derive quantitative spatial features from the day 14, month 3 and month 6 biopsies, including endothelial activation scores, perivascular immune neighbourhood metrics and fibroblast remodelling signatures, and link them prospectively to the subsequent IVUS change between month 3 and month 12. We will aim to produce models that adjust for clinical covariates and integrate the circulating single cell RNA sequencing signals from the matched blood samples. This provides a biologically coherent bridge from tissue level mechanisms in myocardium to arterial remodelling in the coronaries. We will therefore test whether changes in spatial endothelial and perivascular signatures are linked to CAV progression, and whether these are modified in patients receiving TR006.

In short, the myocardial biopsies supply early spatial readouts of vascular inflammation and remodelling, the matched blood provides systemic context and Treg tracking, and both are linked prospectively to IVUS-based CAV progression between month 3 and month 12.

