**Methods and analysis:**

Patients will be recruited from the heart transplant waiting list at Great Ormond Street Hospital. Individualised autologous thymus-derived and expanded Tregs (TR006) will be injected into patients 3–6 months after transplant and follow-up will be conducted as per the post-transplant standard of care protocol with no wean of standard of care immunosuppression. Primary endpoint includes occurrence of Dose-limiting Toxicities in patients receiving TR006. Further data from blood tests, endomyocardial biopsy tissue, coronary imaging and clinical follow-up will be collected.

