### Aims and objectives of ATT-heart

#### Primary objective

To determine the safety of administering a single dose of TR006 in nine children given at 3–6 months post-heart transplant in a planned dose escalation study design.

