**Figure 2 F2:**
[figure not shown]
Schematic to highlight the key events in generating the investigational medicinal product (IMP) TR006 for ATT-Heart. IMP, Investigational Medicinal Product.

Each child will progress through the routine post-operative care pathway (see figure 2). Standard of care immunosuppression will be maintained in all ATT-Heart trial patients and there are no plans to reduce it in this study.

Thymus tissue will be procured prior to the first dose of Basiliximab (anti-CD25 antibody that will affect Treg function) or other induction agent that might be given in theatre. Planned study procedures for ATT-Heart follow routine surveillance including endomyocardial biopsies at 14 days, 3 months and 6 months post-transplant in all patients. At 3 months, in addition to cardiac biopsy, coronary imaging (intravascular ultrasound (IVUS) or coronary angiogram) will be performed in children who weigh more than 25 kg. The outcome from the 3-month biopsy, particularly a negative result for histopathological signs of rejection, will be confirmed prior to administering TR006 to the patient.

Each study patient will receive a single dose of TR006 at 3–6 months post-transplant after initial baseline safety investigations are completed as per the study’s eligibility criteria. They will be monitored in hospital during and after the infusion for one night followed by further safety investigations prior to discharge the next day. Regular study visits as part of the safety monitoring stage will include investigations such as echocardiograms, 12 lead electrocardiograms and blood tests (clinical and research), before and after TR006 dosing. Please refer to onlinesupplemental tables 2  3 for details.

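### The month-6 biopsy is labelled as 3 months after infusion for every child, but the real interval runs from about 0 to just under 3 months, and the biopsy falls inside the IVUS interval it is said to precede

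*Protocol article*

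**What the plan says.** All references are to the protocol article.

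- **Biopsy clock.** Study design schedules "endomyocardial biopsies at 14 days, 3 months and 6 months post-transplant in all patients".
- **Dosing clock.** Study design also states: "Each study patient will receive a single dose of TR006 at 3–6 months post-transplant". The Abstract ("will be injected into patients 3–6 months after transplant") and the Primary objective ("in nine children given at 3–6 months post-heart transplant") give the same window.
- **Order at month 3.** Under Study design, the 3-month biopsy outcome "will be confirmed prior to administering TR006 to the patient", so infusion follows that biopsy.
- **The label.** The Immuno-monitoring specific integrative data analysis plan will use "endomyocardial biopsies at day 14, month 3 and month 6 (ie, 3 months post-Treg infusion".
- **The outcome link.** The same section says "We will derive quantitative spatial features from the day 14, month 3 and month 6 biopsies" and then plans to "link them prospectively to the subsequent IVUS change between month 3 and month 12". It goes on to ask whether the signatures are modified in children who receive TR006.
- **Imaging clock.** Coronary imaging is placed at 3 months after transplant (Study design) and at month 12 after transplant (Study participant recruitment).

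**The concern.** Biopsies and imaging run on the transplant clock, while infusion floats within a three-month window on that clock. The gloss on the month-6 biopsy treats the two clocks as locked together, which is true only for a child dosed exactly at month 3.

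Of the three biopsies named, month 6 is the only one that can fall after infusion; day 14 and month 3 both precede it. It is therefore the only tissue in this plan that can show an effect of TR006 in the graft. Taken literally, the label would pool tissue from a few days to almost three months after infusion as one 3-month readout. Changes within the transplant are part of a stated secondary objective, and the article expects the immune-monitoring data to help choose a dose for phase II.

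The outcome link has a related fault. A feature measured at month 6 cannot precede a change that starts at month 3. Part of any association could reflect vessel change that had already happened when the tissue was taken.

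**Working it through.** **Inputs** (months after transplant)

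- Biopsy B = 6 (Study design).
- Dosing time D between 3 and 6 (Abstract, Primary objective, Study design).
- IVUS change measured from 3 to 12, a length of 12 − 3 = 9 months (immuno-monitoring plan).

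**Step 1. Reproduce the stated figure.** Interval from infusion to biopsy = B − D. The stated 3 months needs 6 − D = 3, so D = 3 exactly.

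**Step 2. Apply the whole dosing window.**

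| Dosed at month | Interval at month-6 biopsy (months) |
|---|---|
| 3 | 3 |
| 4 | 2 |
| 5 | 1 |
| 5.5 | 0.5 |
| 6 | 0 |

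**Step 3. Allow for the wait on the 3-month biopsy result.** The article gives no turnaround time. With an assumed turnaround of t days and 30.44 days per month, the longest possible interval is 3 − t/30.44:

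- t = 7: 2.77 months
- t = 14: 2.54 months
- t = 28: 2.08 months

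At nominal visit times, then, even the earliest-dosed child falls short of 3 months.

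**Step 4. The lower end.** At nominal times the minimum is 0, a tie between dosing and biopsy at month 6. A biopsy before infusion needs dosing at or near month 6 with the routine biopsy done first. The text does not exclude this, but it is a boundary case.

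**Step 5. Position of the month-6 biopsy in the IVUS interval.**

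- Share before the biopsy: (6 − 3)/9 = 33%.
- Share after the biopsy: (12 − 6)/9 = 67%.

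The day-14 biopsy precedes the interval and the month-3 biopsy opens it, so the prospective description fits those two.

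**Step 6. Share of the IVUS interval after infusion**, (12 − D)/9:

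- D = 3: 9/9 = 100%
- D = 6: 6/9 = 67%

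The 100% is a limit, for the reason given in step 3.

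**The case against.** The strongest defence is that the gloss is a nominal label for a child dosed soon after month 3, and that most children may be. Expansion takes up to 23 days, the product is cryopreserved, and dosing is gated on the 3-month biopsy, so the product could be ready by then. Figure 1 and the supplemental visit tables are not shown and may give a target day. This stands as a reason not to assume late dosing. It does not reconcile the text: the article gives a 3 to 6 month window three times, and the gloss equates month 6 with one fixed interval. Later dosing is also conceivable, since the article provides for safety review after the first and last patient of each cohort and bars infusion in suspected rejection. Whether either would delay a given child is inference.

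Several stronger readings are tempting but not supported:

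- **Untreated tissue will routinely be read as treated.** This arises only at the edge of the dosing window.
- **The average interval is 1.5 months, half the stated figure.** That needs dosing spread evenly over months 3 to 6, and nothing in the article suggests it.
- **All change from month 3 to month 6 will be credited to TR006.** The plan places control and Treg-arm biopsies on the same slide and describes covariate-adjusted models. It states no rule of uncontrolled attribution.
- **The blood analysis has the same fault.** Blood sampling is described as before and after infusion, and follow-up visits are counted from dosing.

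A further defence is that classification rules belong in a fuller document. That would answer a complaint of missing detail. Here the article states an interval and a time order that its own schedule contradicts.

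**Conclusion.** The point holds as a mislabelled exposure time and a misdescribed time order. The month-6 biopsy lies from about 0 to just under 3 months after infusion, not uniformly at 3 months, with a possible pre-infusion sample only at the boundary. One third of the month 3 to 12 IVUS change precedes that biopsy, and between 67% and 100% of it follows infusion.

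These ranges rest only on the stated schedule and nominal visit times. The 2.08 to 2.77 month ceilings also rest on assumed turnaround times. The distribution of actual dosing dates is unknown, so no typical interval can be given.

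This should be fixed, but it is not critical. It affects the spatial tissue analysis and its link to vasculopathy in a trial of nine children that does not claim to quantify efficacy. The primary endpoint of dose-limiting toxicities is unaffected, and no escalation decision described in the article uses these biopsies.

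**What to change.** Change the analysis text only; dosing and biopsy timing stay as they are.

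1. Reconcile the immuno-monitoring plan with Study design by removing the 3-month gloss and calling the sample the month-6 post-transplant biopsy.
2. Classify each month-6 biopsy as pre- or post-infusion from actual dates.
3. Report actual days from infusion to biopsy for each child, and use them in the spatial analysis of TR006 effect. Control samples have no infusion date, so comparisons with them should stay on time since transplant.
4. Describe the link between month-6 features and the month 3 to 12 IVUS change as partly concurrent, and keep the word prospective for day-14 and month-3 features. State each child's share of the IVUS interval that follows infusion.

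The cost is a few sentences and the use of infusion and biopsy dates, which the trial should hold in any case. The downside is that fewer samples will count as a 3-month post-infusion readout.

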**Trial registration number:**

ISRCTN15374803.

STRENGTHS AND LIMITATIONS OF THIS STUDYAll eligible patients waitlisted for heart transplant (in one of the only two centres in the UK that perform paediatric heart transplant) will be approached and prospectively recruited and followed up in this study to minimise selection bias.As a phase I trial with primary focus on establishing safety of the cellular therapy at a range of doses, the study participants will not be randomised (or blinded) and results will not be able to quantify biological efficacy of Treg on cardiac allograft vasculopathy in a small population of patients with statistical significance.However, the immuno-monitoring schedule and analysis of data from patient biospecimens (collected before and after delivery of the therapy) will seek to study how the immune system of patients changes with cellular therapy administration to provide further information about the biological effect of the Tregs (which can be studied further in future studies).

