## Methods and analysis

### Study design

This is a phase I, open label, single-centre clinical trial investigating two different dose banding ranges (1–3×10^6^ cells/kg and 5–10×10^6^ cells/kg) of autologous thymus derived Tregs (TR006) in nine paediatric heart transplant recipients. All clinical and patient-facing activity (including dosing) will occur at GOSH in London, UK.

When a suitable organ is available for a recruited study patient (see figure 2), their thymus tissue will be collected during surgery. This tissue will be transported to the GMP Facility at Guy’s Hospital National Health Service (NHS) Foundation Trust and will form the starting material for the IMP production under GMP conditions, as outlined in the manufacturing section below.

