#### Data analysis plan

Demographic data and baseline characteristics will be summarised to describe the populations analysed in this study (both all participants and participants administered at each dose level). Response will be reported descriptively based on the per-protocol population. Time to first response will be summarised by Kaplan-Meier curve. Median time to event estimation as well as the associated 95% CI will be reported. All other secondary endpoints will be summarised by rates and corresponding 95% CIs.

Interim safety data will be reviewed after dosing of the first and last patient of each cohort, with interim analyses provided to the Data Monitoring Committee (DMC) in order for decisions related to the next patient cohort to be made. This is particularly in relation to any safety concerns, or DLTs, prior to confirming progression of the dose escalation for the next cohort. In addition, the DMC will be informed of any Serious Adverse Reactions or Suspected Unexpected Serious Adverse Reactions (SUSARs) as they occur. All safety data will be analysed descriptively. Statistical comparisons between patient populations are unlikely to be used, but if needed, a 5% level of significance will be used.

Study data will be pseudo-anonymised and will be stored on a password protected computer at GOSH. Clinical data will be transcribed from the medical notes and source data sheets to the study-specific recording system. All data will be stored in line with UK General Data Protection Regulation and UK Data Protection Act 2018.

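### The immuno-monitoring plan refers to a control arm and a test of modification by TR006, but all nine planned participants are dosed, so TR006 versus no TR006 cannot be estimated from the trial's own participants

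*Protocol article*

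**What the plan says.** The design is described consistently in several places. The Study design section opens with "This is a phase I, open label, single-centre clinical trial investigating two different dose banding ranges" and continues "of autologous thymus derived Tregs (TR006) in nine paediatric heart transplant recipients". Later in the same section, after Figure 2, it states: "Each study patient will receive a single dose of TR006 at 3–6 months post-transplant". The dose escalation section adds: "A single ascending dose design will be followed with groups of three patients in three cohorts". The strengths and limitations box says that participants are neither randomised nor blinded, and that efficacy on CAV cannot be quantified with statistical significance.

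The section headed Immuno-monitoring specific integrative data analysis plan reads differently. On biopsy processing it says: "We will place control and Treg arm biopsies on the same slide to control for batch effects". It then commits to testing whether changes in endothelial and perivascular signatures are linked to CAV progression, and "whether these are modified in patients receiving TR006". The Data analysis plan says "Statistical comparisons between patient populations are unlikely to be used", with a 5% significance level held in reserve.

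**The concern.** A slide layout with a control arm and a Treg arm, followed by a test of modification in those who received TR006, describes a two-group comparison. The rest of the article describes one group. This is not detail that a condensed article has left out: the article states a comparison that its own stated design does not supply.

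Two things are at stake. If nobody resolves the wording, the planned test cannot be run as described. If it is resolved informally later, biopsies from some other source may be brought in without stated eligibility, timing or matching, and a difference from them may be credited to TR006. The slide layout also has to be fixed before the assays are run and cannot be changed afterwards.

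**Working it through.** **1. Count of treated and untreated participants.** The dose escalation section gives three cohorts of three: 3 + 3 + 3 = 9. This reproduces the nine in the primary objective and in Study design. All nine are to be dosed, so untreated = 9 − 9 = 0.

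**2. Other uses of the word control.** The control groups in the background sections belong to other studies: a renal transplant trial, and a thymus-derived Treg study with four untreated children. In Table 1, control means third-party antigen in the alloreactivity assay. None of these is a source of biopsies for this trial.

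**3. Between-patient model.** The article writes out no model. The simplest one that expresses the stated test is

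CAV change = a + b·TR006 + c·signature + d·(TR006 × signature).

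With TR006 = 1 for all nine, the TR006 column equals the intercept and the interaction column equals the signature column. The design matrix has rank 2 out of 4. Only a + b and c + d can be estimated; b and d cannot. The association c + d among treated children is estimable without a control.

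**4. Within-patient model.** The biopsies are at day 14, month 3 and month 6, and the article treats month 6 as the post-infusion one. Take 9 patient effects, 2 time contrasts and 1 post-infusion indicator, which makes 12 columns. If every child is dosed between the month 3 and month 6 biopsies, the indicator is identical to the month 6 column, so the rank is 11 out of 12. A before/after change can be described but cannot be separated from time since transplant. If a child happened to be dosed after the month 6 biopsy, the columns would separate formally, but only through unplanned differences in dosing time.

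**5. Exposure at the month 6 biopsy.** The integrative plan describes this biopsy as three months after infusion. Study design allows dosing anywhere in months 3–6. Time from infusion to biopsy = 6 − month of dosing: dosing at month 3 gives 3 months, month 4 gives 2, month 5 gives 1, and month 6 gives about 0. The before/after contrast is therefore not uniform across children.

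**6. CAV change.** It runs from month 3 to month 12, with one image before infusion. There is no pre-infusion slope against which to judge the later change.

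**7. What an external control could show (illustration).** The article gives no number of controls, so 4, 9 and 18 are assumptions. For a two-sample t test at 5% (two-sided assumed, as the article does not say) with 80% power, solve for the standardised difference D in

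0.80 = 1 − F(t₀.₉₇₅; df, δ), with δ = D·√(n₁n₂/(n₁+n₂)), df = n₁+n₂−2,

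where F is the noncentral t distribution function and n₁ = 9.

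| Controls (assumed) | df | √(n₁n₂/(n₁+n₂)) | Detectable D | δ |
|---|---|---|---|---|
| 4 | 11 | √(36/13) = 1.66 | 1.85 | 3.08 |
| 9 | 16 | √(81/18) = 2.12 | 1.41 | 2.99 |
| 18 | 25 | √(162/27) = 2.45 | 1.19 | 2.91 |

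A defined comparator would make the contrast estimable. Only very large differences would be detectable, and the comparison would still be non-randomised.

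**The case against.** The strongest reply is that this is a condensed article, and the full protocol, available on request, may define the controls. Biopsies at these times follow routine surveillance, so matching non-trial biopsies could exist. Families may also withdraw before dosing and still supply routine data, so enrolled but undosed children are conceivable. This stands as far as it goes: the article does not prove that no comparator exists anywhere. It does not remove the contradiction, because every description of the design here is of nine treated children, and none of these possible sources is linked to the control wording.

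A second reply is that modification by TR006 could mean change within a patient or a contrast between dose bands, and that Table 1 frames pharmacodynamics as longitudinal comparison by dose. Those analyses are possible, but they do not fit a sentence that sets a control against a Treg arm.

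A third is that the article already disclaims efficacy and expects few comparisons between populations. That limits the risk of a confirmatory claim. It supplies no comparator, and it sits awkwardly beside a section that says it will test the question.

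Some stronger readings are tempting but unsupported:

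- A reader might infer that outside controls would be sicker. No control is described, so the direction of any bias is unknown, and a control with a month 6 biopsy must also have survived to that point. What can be said is that dosed children are selected on a negative 3-month biopsy and a releasable product.
- A reader might measure the problem by the correlation that nine children could detect. That concerns the association among treated children, which needs no control.
- A reader might conclude that the covariate-adjusted models should go. They are stated only as an aim, and this point does not require their removal.

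**Conclusion.** The point holds in a limited form. With 9 treated and 0 untreated participants planned, the effect of TR006 versus no TR006 on the spatial signatures, or on their link with CAV, cannot be estimated from the trial's own participants. The article states such a comparison without a source for it.

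A reader might go further and infer that the trial can say nothing about TR006 and these signatures. The documents do not support that. Three descriptive analyses remain: change within patients, description by dose band (3 children in the lower band and 6 in the higher, if escalation proceeds as planned), and the signature–CAV association among treated children. The first is confounded with time since transplant and has between about 0 and 3 months of exposure at the month 6 biopsy.

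The conclusion assumes that all nine planned participants are dosed as stated and that the control wording means untreated children. The defect is confined to the immuno-monitoring analysis and does not touch the primary dose-limiting toxicity endpoint.

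**What to change.** Choose one of two routes before slides are laid out.

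**(a) No controls intended.** Remove the control-arm wording and the test of modification by TR006. State instead an exploratory, descriptive analysis of:

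- within-patient change (day 14 and month 3 versus month 6);
- results by dose band;
- the signature–CAV association among treated children.

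Say that before/after change cannot be separated from time since transplant, and report each child's actual time from infusion to the month 6 biopsy. Rewrite the slide-layout sentence to say which contrast it protects: keeping a child's serial biopsies on one slide protects within-patient change but ties slide to patient for comparisons between children.

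**(b) Non-trial or undosed controls intended.** Name their source. Apply the same eligibility and landmark as for dosed children, including a negative 3-month biopsy and the same time since transplant. Label the contrast descriptive and non-randomised.

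Route (a) costs wording only. Route (b) also requires the comparator to be specified. In both cases the price is giving up a causal claim about TR006 that this design cannot support.
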